### Patients

We will include patients from the age of 2 treated in the 25-bed PACU after surgery on workdays in one of the following specialties: neurosurgery, orthopaedic surgery, trauma surgery or ear-nose-throat (ENT) surgery. Patients are excluded from the study if they are not permitted oral intake of fluids or food including those with swallowing difficulties or other contraindications to safe oral consumption, or if they are transferred to an intermediate or intensive care unit postoperatively. Both elective and emergent procedures are included.

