Every morning, the study day is randomised via a web-based randomisation tool (studyrandomizer.com, Rotterdam, Netherlands).(Study Randomizer 2017) Study days are randomized in a 1:1 ratio using permuted blocks with variable block sizes ranging from 2 to 6. The researcher collecting the data is blinded to randomisation details (e.g., blocking). On intervention days, ice-lollies are offered to all eligible patients by the nursing staff in addition to standard of care refreshments at the same time point at which oral fluids are routinely offered, and always at nurse discretion. Patients must be sufficiently awake and able to safely hold and swallow oral intake. No formal recovery score threshold is applied. On control days there is standard of care without ice-lollies. Standard postoperative refreshments in our institution include water, coffee and biscuits. Nurses are notified of the randomisation result by personal communication and a large sign in the middle of the PACU. To ensure protocol adherence and prevent cross-contamination, the freezer is kept securely locked on control days when no ice-lollies are provided. Adherence to the intervention will be documented. On intervention days, it will be recorded whether an eligible patient was offered and consumed an ice lolly. Patients who decline the ice lolly despite being eligible will remain in the intention-to-treat analysis according to the randomized day. A per-protocol analysis will additionally be performed including only patients who received the allocated intervention as planned. Anonymised patient data is entered prospectively at the bedside by a dedicated study investigator directly into a password-protected electronic Case Report Form (eCRF) hosted on the secure intranet server. Access is restricted to the research team and all activities are logged. No direct personal identifiers (e.g., name, hospital number, case number) are recorded. K-anonymisation is ensured by generalization via binning (age, height, weight, procedure) in predefined ranges. Data completeness is monitored during entry with immediate correction of missing or implausible values. Data collection ends when the patient is discharged to the general ward without follow-up. Patients are not re-identifiable in the study database.

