#### Secondary outcome

Three secondary outcomes have three main components: pain, nausea and vomiting, and delirium. Pain includes the visual analogue scale at admission and discharge, and consumption of pain medication such as opioids, NSAID, metamizole and paracetamol. Nausea and vomiting is documented as separate outcomes, in addition the administration of any antiemetic medication intra- or postoperatively is recorded. Delirium is defined as a Nursing Delirium Screening Scale (NUDESC) at discharge ≥ 2. The NUDESC is also the communicated primary outcome to the staff and study team involved in data collection.

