#### Statistical analyses

After patient enrolment is finished, data will be analysed. There is no interim analysis planned due to the short study period. Patient characteristics and clinical data will be descriptively analysed as appropriate after visual normality check. The proportion of missing data is expected to be very low, as data are entered prospectively at the bedside by a dedicated study investigator. If missing data remain minimal, a complete-case analysis will be performed. If the proportion of missing data should exceed expectations, appropriate sensitivity analyses will be considered. The analysis will be conducted as Intention-to-Treat (ITT) in all randomized patients according to group assignment and Per-Protocol (PP) with all patients who received the assigned intervention as planned. All tests will be two-sided, with α = 0.05.

Baseline characteristics will be summarised descriptively by treatment group. Continuous variables will be reported as mean (standard deviation) or median (interquartile range), as appropriate. Categorical variables will be presented as counts and percentages. No formal statistical testing of baseline differences will be performed.

To account for the cluster-randomized design with randomization at the level of the day, all inferential analyses will be performed using mixed-effects regression models including a random intercept for cluster (day).

For the primary outcome (PACU length of stay), a linear mixed-effects model will be used. If substantial deviation from normality is observed, an appropriate generalized linear mixed-effects model (e.g., gamma distribution with log link) will be applied. Binary outcomes will be analysed using generalized linear mixed-effects models with logit link.

For medication dosage outcomes with a high proportion of zero values, a two-part modelling approach will be applied: first, a mixed-effects logistic regression model will analyse the probability of receiving any medication (yes/no); second, among patients receiving medication, dosage will be analysed using an appropriate mixed-effects model depending on distributional characteristics.

For the primary and secondary outcomes, age range, sex, ASA physical status, surgery type, and duration and type of anaesthesia will be included as covariates. For the secondary outcomes pain medication and nausea/vomiting, the duration of stay in the PACU is included as an additional covariate.

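### The medication-dose models leave out the recorded body-weight range, a small and avoidable loss of precision in one secondary outcome

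*Protocol article*

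**What the plan says.** Four statements in the protocol article bear on this.

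- **Population (Patients):** "We will include patients from the age of 2". No upper age limit is given.
- **Outcome (Secondary outcome):** the pain component includes "consumption of pain medication such as opioids, NSAID, metamizole and paracetamol". The dose unit is not stated.
- **Model (Statistical analyses):** dosage outcomes with many zeros get a two-part model. The first part is a mixed-effects logistic model for receiving any medication. In the second part, "among patients receiving medication, dosage will be analysed using an appropriate mixed-effects model depending on distributional characteristics".
- **Covariates (Statistical analyses):** "age range, sex, ASA physical status, surgery type, and duration and type of anaesthesia will be included as covariates". One outcome-specific addition follows: "For the secondary outcomes pain medication and nausea/vomiting, the duration of stay in the PACU is included as an additional covariate".

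Weight is available as a category. The Protocol section says that "K-anonymisation is ensured by generalization via binning (age, height, weight, procedure) in predefined ranges". Weight appears in neither covariate statement, and no scaling of dose by weight is mentioned.

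**The concern.** Body size can influence the amount of analgesic given, and the population runs from toddlers to the elderly. A baseline variable that predicts the outcome and is already in the database normally belongs in the adjustment set. The article considered the covariates outcome by outcome, since it adds PACU stay for pain medication, but it left weight out of the dose model.

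Age range and sex stand in for body size only on average. Two adults of the same sex and age band can differ widely in weight, as can two children in one band. Any dose variation that follows this difference stays in the residual and widens the confidence interval for the effect of the intervention on dose among recipients. What is at stake is the precision of that one estimate.

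**Working it through.** **No figure in the plan to reproduce.** The sample-size section concerns PACU stay only. The article gives no variance, effect or power for medication dose, so the size of the loss can only be illustrated.

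**Which analyses are touched**
- Dose among recipients: directly, because the outcome is an amount.
- Any medication (yes/no): essentially not, because it is not an amount.
- Pain scores and PACU stay: essentially not, because neither is a dose.

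**Bias or precision.** Weight is a baseline variable, and randomising days balances it in expectation. Leaving it out therefore does not shift the estimated effect. The second part looks only at recipients, so this reasoning carries over as long as the intervention does not change which body sizes receive medication. Nothing in the article suggests that it does.

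**Illustration: assumed inputs, none from the article**
- Share of children: 2%, 5%, 10% or 20%. Ages are uniform within 2–18 and 18–90 years.
- Child weight: (8 + 3 × age) kg with log-SD 0.15. Adult weight: 70 or 84 kg by sex with log-SD 0.18.
- Log-SD of individual analgesic need: 0.5.
- Child dose proportional to weight. Adult dose proportional to weight to the power 0 (fixed), 0.5 (partly scaled) or 1 (fully proportional).
- Seven age bands (cut at 6, 12, 18, 40, 60 and 75 years) and 10-kg weight bins.

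The quantity is the ratio V2/V1. V1 is the residual variance of dose after age band and sex, and V2 is the residual variance after age band, sex and weight bin. Ranges run over the four shares of children, in 400,000 simulated patients per scenario.

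| Adult dosing assumed | V2/V1, raw dose | V2/V1, log dose | Fall in residual variance |
|---|---|---|---|
| Fixed | 0.994–1.000 | 0.976–0.998 | about 0–2% |
| Partly scaled | 0.966–0.973 | 0.949–0.968 | about 3–5% |
| Fully proportional | 0.898–0.902 | 0.884–0.889 | about 10–12% |

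**How much age and sex already do.** With fixed adult doses, nearly all size-driven variation is the child-adult gap and the spread among children. With 20% children, age band and sex explain 0.318 of log-dose variance, and adding weight raises this to 0.335. So 0.318/0.335 = 95% of what can be explained is already taken. On the raw scale it is 0.151/0.156 = 97%.

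**Hand check on the log scale, adults within one age band and sex.** The share of variance due to weight is k²·0.18²/(k²·0.18² + 0.5²), where k is the power above.
- k = 1: 0.0324/(0.0324 + 0.25) = 11.5%.
- k = 0.5: 0.0081/(0.0081 + 0.25) = 3.1%.
- k = 0: 0%.

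These agree with the table. Larger variation in individual need would shrink the gain.

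**In terms of the standard error.** If the residual variance dominates, the standard error is multiplied by the square root of the ratio.
- Ratio 0.98: √0.98 = 0.990, about 1% narrower.
- Ratio 0.97 to 0.95: 0.985 to 0.975, about 1.5–2.5% narrower.
- Ratio 0.90 to 0.88: 0.949 to 0.938, about 5–6% narrower.

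The illustration leaves out ASA status, surgery type, anaesthesia variables, PACU stay and variation between days. All of these could reduce the gain further.

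**The case against.** The strongest reply is that this is a preference about one more precision covariate. Nothing in the article is contradictory. The dose unit is the kind of detail an article leaves to the full protocol or the SAP, which the article says is available on request. Dose may already be scaled by weight there, and the covariate list is not declared exhaustive. Age range and sex are in the model, and the remaining gain may be close to nil.

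Most of that stands, and it is why the point is minor. It does not remove the point. The article does not defer the covariates: it lists them, and it adds one specifically for pain medication without naming a relevant variable that is already recorded.

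A reader might also infer stronger claims that the article does not support.

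- **Large patients dominate the effect in milligrams.** With assumed weights of 12 kg and 75–100 kg, a 10% saving would be 75/12 = 6.25 to 100/12 = 8.3 times smaller in a child. This needs an additive model in milligrams. The article states no unit and leaves the dose model open to its distribution. For PACU stay it names a gamma model with log link as the alternative, and under a log link a 10% reduction is the same ratio at every body size.
- **The gain is 4–16%.** That follows from r² with r = 0.2 to 0.4 (0.04 and 0.16), but only if r is the correlation of weight and dose left after the listed covariates. The article gives no r, and the upper end exceeds even the fully proportional scenario above.
- **Earlier evidence in children makes this pressing.** The Discussion says that the paediatric tonsillectomy study found lower pain scores but no difference in pain medication, which is the outcome at issue here.

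**Conclusion.** The point holds as a minor matter of precision. Weight is recorded in ranges and patients span a wide range of body size, yet the stated covariates for the dose model omit weight. Some weight-driven spread within age bands can therefore stay in the residual of the dose-among-recipients model.

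The size is unknown. On the assumed inputs the avoidable residual variance is about 0–2%, 3–5% or 10–12%, depending on how far adult doses follow weight. Even the top of that range narrows the standard error by only about 5–6%. The figures rest on the assumed variation in weight and need, the assumed bin widths, and a dose that the SAP does not already scale by weight.

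The article does not support a reading of bias, or of any threat to the primary result.

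**What to change.** Before the analysis starts, add one sentence to the SAP: the recorded weight range enters as a categorical covariate in the second-part (dose among recipients) models, alongside the covariates already listed. The data are already held. The cost is a few degrees of freedom, one fewer than the number of weight ranges. Sparse ranges can be merged by a rule set in advance. Overlap between weight range and age range in children makes those two coefficients hard to read separately, but does not harm the estimate of the intervention effect.

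Optionally, in the exploratory subgroup aged 12 years or younger, report dose per kg computed from the midpoint of the weight range and labelled as approximate.

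A new eCRF field holding exact dose per kg is not advised. Placed beside the dose, it would reveal exact weight by division and so undo the weight binning. It would also come too late, since the Trial status section expected recruitment to end in February 2026 and the article appeared in March 2026.

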## Background

In the post-anaesthesia care unit (PACU), healthcare staff provide close observation and supportive care until patients regain stable vital signs and are sufficiently alert. Effective management in the PACU is essential to ensure patient safety, comfort, and timely progression through the surgical care pathway. After undergoing anaesthesia, many patients experience side effects such as nausea, vomiting, sore throat, hoarseness, dizziness, and disorientation. These symptoms can delay recovery and prolong the time needed before patients can safely return to their hospital ward or be discharged. Amongst the most common complaints after anaesthesia are sore throat or hoarseness. (Lehmann et al. 2010; Maruyama et al. 2004) Ice-lollies are a non-pharmacologic intervention in the PACU after surgery. They may have a beneficial effect on recovery: the temperature serves as cryotherapy, holding an ice lolly requires attention and keeps patients busy, ice lollies are often associated with positive childhood memories that can take away the focus from boredom, pain and nausea. There is limited evidence that this intervention reduces pain and emergence agitation in children after oral surgery (Sylvester et al. 2011) (Liang et al. 2023) However, if ice-lollies speed up recovery leading to faster discharge to the ward in a general surgical population is unclear. Therefore, we designed a prospective, single blinded monocentric trial investigating the effect of ice-lollies in the PACU on patients' length of stay. The hypothesis is that offering ice-lollies to postoperative patients leads to a faster recovery from the side effects of anaesthesia, thereby reducing the length of stay in the PACU. Secondary outcomes are the effect on consumption of pain medication, nausea and vomiting, and postoperative delirium.

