### Outcomes

#### Primary outcome

The primary outcome is the time spent in the PACU from admission after surgery to the decision to discharge by the attending nurses and physicians. Time of decision to discharge instead of time of discharge was chosen to avoid procedural delays of patient transfer to the general ward due to staff shortage. PACU discharge is based on a standardized and routinely documented clinical assessment. This includes evaluation of respiratory and circulatory stability, temperature, urine output, bleeding, nausea/vomiting, sensibility and motor function, as well as neurological status assessed using the Glasgow Coma Scale, the Richmond Agitation-Sedation Scale, and the NUDESC score. Patients are discharged to the ward once all parameters are within acceptable clinical limits according to institutional practice.

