The effect of the intervention in our study on secondary outcomes has been shown in preliminary studies by other researchers. A study in 92 children undergoing tonsillectomy randomised to receive an ice-lolly after anaesthesia observed lower pain scores in the intervention group, but no difference in pain medication administration. (Sylvester et al. 2011) In our study, all age groups are included. To find out, whether the cold reduces pain in ENT-surgery patients only, suggesting a local anaesthetic effect, we analyse the effect on surgical subgroups separately. If ice-lollies show a beneficial effect over all ages and surgical procedures, the benefit of the intervention seems to be a central anti-nociceptive effect such as positive memories or distraction from negative feelings. Another secondary outcome is nausea and vomiting. Some team members may be concerned, that oral intake of 55 ml of frozen, orange-flavoured liquid may lead to an increased rate in nausea and vomiting. A recent meta-analysis showed a beneficial effect of early postoperative fluid intake on nausea without an increase in vomiting. (M R Kang et al 2025) However, usually only water is offered to patients, therefore the analysis of postoperative nausea and vomiting is important in our study to detect possible negative side effects. The third secondary outcome is the effect on postoperative delirium reflected by the routinely assessed NUDESC at discharge from the PACU. Another study demonstrated a vast reduction of emergence delirium in children after oral surgery when they received an ice-lolly.(Liang et al. 2023) In our study, delirium was communicated as primary outcome to the staff in the PACU and the investigators who collect the anonymized patient data. Thereby, we avoid bias towards the primary outcome (Hawthorne effect), which is a strength of our study. Since we also include orthopaedic surgery with many elderly and frail patients, the analysis of this outcome might offer valuable insight into a non-pharmacological prevention strategy of postoperative delirium in an adult patient group.

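### Adjusting the pain-medication and nausea/vomiting models for PACU stay, the trial's own primary outcome, can distort the estimated effect of ice-lollies on these secondary outcomes

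*Protocol article*

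**What the plan says.** The Statistical analyses section lists covariates known before PACU admission for all outcomes (age range, sex, ASA status, surgery type, duration and type of anaesthesia). It then adds one more for two secondary outcomes: "For the secondary outcomes pain medication and nausea/vomiting, the duration of stay in the PACU is included as an additional covariate". It gives no reason for this, defines no direct-effect estimand and mentions no parallel model without stay.

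Four other statements bear on that choice:

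- Outcomes, Primary outcome: "The primary outcome is the time spent in the PACU from admission after surgery to the decision to discharge". The added covariate is therefore the primary outcome.
- Background: the hypothesis is that the lolly speeds recovery from side effects, "thereby reducing the length of stay in the PACU".
- Background, after naming nausea and vomiting among the side effects: "These symptoms can delay recovery and prolong the time needed before patients can safely return to their hospital ward or be discharged". The discharge assessment under Primary outcome also covers them: "This includes evaluation of respiratory and circulatory stability, temperature, urine output, bleeding, nausea/vomiting, sensibility and motor function".
- Discussion, on the purpose of the nausea/vomiting outcome: "the analysis of postoperative nausea and vomiting is important in our study to detect possible negative side effects".

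**The concern.** Covariates in a randomised comparison should not be affected by treatment. PACU stay is measured after randomisation, and changing it is the aim of the trial.

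For nausea/vomiting, stay also lies downstream of the outcome being modelled. Among patients with equal stay, those on lolly days have been speeded up by the lolly, so they must have had more of whatever slows discharge, including nausea. Holding stay fixed can thus create a link between lolly and nausea that randomisation had excluded.

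For pain medication, a shorter stay may itself mean fewer doses, and adjustment takes that part out of the estimate.

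At stake is the interpretation of two of the three secondary outcomes. One of them is the outcome the Discussion uses to look for side effects, which is a question about the total effect of offering the lolly.

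**Working it through.** The documents give no figure for this bias, so there is none to reproduce. The check has three parts.

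**1. Nausea/vomiting, by formula**

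Inputs from the Sample size section: SD of stay 40 min (variance 1,600), planned shortening 4.5 min, 3,140 patients. Assumed, not in the documents: nausea in 20% of patients, and nausea adding a = 10 to 40 min to stay. Let d be the shortening that does not run through nausea.

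Take stay as normal given arm and nausea, with residual variance s² = 1,600 − a² × 0.2 × 0.8. By Bayes' rule, the log odds of nausea given stay and arm equal the log odds given arm plus the log likelihood ratio of the observed stay. The arm coefficient is then

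log OR (adjusted) = log OR (true) + a × d / s².

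With d = 4.5 and a true OR of 1.00:

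| a (min) | s² | a × d / s² | adjusted OR |
|---|---|---|---|
| 10 | 1,584 | 45/1,584 = 0.028 | 1.03 |
| 20 | 1,536 | 90/1,536 = 0.059 | 1.06 |
| 30 | 1,456 | 135/1,456 = 0.093 | 1.10 |
| 40 | 1,344 | 180/1,344 = 0.134 | 1.14 |

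The added term is zero when d = 0, whether the lolly leaves stay unchanged or shortens it only through nausea. Halving d to 2.25 min halves the log-scale shift: the ORs become 1.01, 1.03, 1.05 and 1.07.

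**2. Nausea/vomiting, by simulation**

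- *No true effect on nausea, d = 4.5.* In 3,000 simulated trials of 3,140 patients per scenario (individual level, no clustering), the mean adjusted ORs were 1.03, 1.06, 1.10 and 1.14. The nominal 5% test rejected in 7%, 10%, 17% and 27%. Without stay in the model the OR was 1.00 and rejection 4–6%.
- *True benefit.* In a run of one million patients (control log odds −1, a shared frailty term, d = 4.5), a marginal OR of about 0.81 became 0.84, 0.88 and 0.91 for a = 10, 20 and 30.
- *No effect on anything.* The adjusted OR was 1.00.
- *Benefit on the symptom only, d = 0.* The OR stayed at about 0.81. In this scenario stay fell by only about 0.5 to 1.1 min.

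**3. Pain medication, by structure**

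The total effect on medication is the part at fixed stay plus the part that arises because stay changes. The planned model reports only the first. Even that part is a clean direct effect only if nothing unmeasured drives both stay and medication. The documents do not relate dosing to minutes of stay, so no size can be given. Neither pain nor analgesia is named in the discharge assessment, so the reverse path shown for nausea/vomiting is not documented here.

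**The case against.** **The bias is conditional.** A reader might infer that these effects are biased whatever happens, or that the randomised comparison is lost. The documents do not support that. The Background hypothesis runs through recovery from side effects, and if nausea were the only route there would be no bias. This stands as a limit on the claim, but it does not remove it. The Discussion names routes that bypass nausea: cold as a stimulus against residual sedation, and distraction from boredom and pain. Relief of other side effects bypasses nausea as well. Under the 20% assumption, abolishing nausea altogether would save 0.2 × 10 = 2 min or 0.2 × 20 = 4 min on average, less than 4.5 min. At 30 or 40 min (6 or 8 min saved) a route through nausea alone would need 4.5/6 = 75% or 4.5/8 = 56% of cases to be prevented.

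**The size rests on assumptions.** This stands. The 27% rejection rate needs nausea to add 40 min and the whole 4.5 min to bypass it. The calculations also omit the day effect and the baseline covariates.

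**Stay is exposure time.** More minutes mean more chances to be dosed or to vomit. That is a recognisable motive, though the article does not state it. A difference in exposure caused by the lolly is part of its effect, and a supplementary rate can describe it.

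**Harm could be hidden.** A reader might infer that the model masks harm. For a shortened stay the shift is the other way: towards a false alarm or an understated benefit. The Discussion speaks of detecting side effects, not of ruling them out.

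**The two-part dose model.** A reader might add as an error that the second part compares only recipients: "second, among patients receiving medication, dosage will be analysed using an appropriate mixed-effects model depending on distributional characteristics". Two-part models are a standard choice for data with many zeros, and the first part compares all randomised patients. It is enough to note that the recipients-only part is not a randomised comparison and should not be read alone. For example, suppose 40 of 100 controls are dosed, half with 5 mg and half with 10 mg, and the lolly spares five patients the 5 mg dose. The mean among recipients rises from 7.5 to 275/35 = 7.9 mg, while the mean over all patients falls from 3.0 to 2.75 mg.

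**Secondary outcomes of a study that calls itself exploratory.** True, and this limits the weight of the point.

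**Conclusion.** The concern holds in a conditional form. The plan adjusts two secondary outcomes for a variable that the intervention is meant to change and, for nausea/vomiting, that the outcome itself influences. If the lolly shortens stay by any route other than the modelled symptom, the nausea/vomiting estimate moves towards harm or a smaller benefit. The range of 1.03–1.14 for a true odds ratio of 1.00, with 7–27% rejection, illustrates this under stated assumptions and does not predict the trial's result. For pain medication the argument is narrower: the total effect is not estimated if any of it runs through a shorter stay, and no size can be given. The primary analysis and the delirium model are untouched.

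**What to change.** Remove PACU stay from the main pain-medication and nausea/vomiting models and keep the pre-PACU covariates already listed. If exposure time is of interest, report a stay-adjusted or per-hour analysis as supplementary, labelled as such and with a statement of what it estimates. Add a note that the recipients-only dose results are to be read together with the any-medication results.

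The change costs one sentence and needs no new data. Recruitment was expected to end in February 2026, before the article appeared, so the change should be made as a dated amendment with its reason, preferably before the arms are compared.

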Prespecified subgroup analyses are performed based on age (≤ 12 years and ≥ 75 years), sex, ASA classification, type of anaesthesia and surgery type (neurosurgery, orthopaedic surgery, ENT, plastic surgery). Subgroup analyses are considered exploratory.

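### The surgery-type subgroups do not match the eligible specialties, and analysing specialties separately does not test whether a pain effect is confined to ENT patients

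*Protocol article*

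**What the plan says.** The Patients section limits inclusion to "neurosurgery, orthopaedic surgery, trauma surgery or ear-nose-throat (ENT) surgery". The subgroup paragraph of Statistical analyses names "surgery type (neurosurgery, orthopaedic surgery, ENT, plastic surgery" and adds: "Subgroup analyses are considered exploratory".

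The same section makes surgery type an adjustment variable for the primary and secondary outcomes: "age range, sex, ASA physical status, surgery type, and duration and type of anaesthesia will be included as covariates". It names no interaction between treatment and surgery type.

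The Discussion gives the surgical subgroups a specific job: "To find out, whether the cold reduces pain in ENT-surgery patients only, suggesting a local anaesthetic effect". The method it names is: "we analyse the effect on surgical subgroups separately". The opposite result is tied to a central mechanism: "If ice-lollies show a beneficial effect over all ages and surgical procedures".

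**The concern.** There are two separate problems.

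First, the lists disagree. Each has four entries and they differ in one: trauma surgery is eligible but is not a subgroup, and plastic surgery is a subgroup but is not eligible. Trauma may be meant to fall under orthopaedics, or plastic cases may in fact be recruited, but the article says neither. The categories of the surgery-type covariate are not spelled out, so the mismatch also leaves the coding of that adjustment variable open.

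Second, the question and the method do not fit. That an effect occurs in ENT patients only is a claim about a difference between specialties. Separate results answer a different question, namely whether there is evidence of an effect within each specialty. If those results are sorted by significance, specialties with the same true effect will often look different, and the Discussion would attach a mechanism to that pattern.

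**Working it through.** **Comparison of the lists**

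| Specialty | Eligible (Patients) | Subgroup (Statistical analyses) |
|---|---|---|
| Neurosurgery | yes | yes |
| Orthopaedic | yes | yes |
| ENT | yes | yes |
| Trauma | yes | no |
| Plastic | no | yes |

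**Inputs for the illustration.** The plan states no figure for the subgroups. From the Sample size section: difference 4.5 min, SD 40 min, two-sided α 0.05, power 80%, about 30 patients per day, ICC 0.01, total 3,140. Assumed here, because the documents do not give it: four populated specialties of equal size, and the same true effect in each. The effect is that for length of stay, since none is given for pain.

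**Whole trial.** The standardised effect is 4.5/40 = 0.1125 and the design effect is 1 + 29 × 0.01 = 1.29. The effective number per arm is 1,570/1.29 = 1,217, so SE = √(2/1,217) = 0.0405. Power is Φ(0.1125/0.0405 − 1.96) = 0.79, in line with the stated 80%.

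**One specialty analysed alone, two ways**
- Scaling from 80% power: the whole-trial non-centrality is 2.80. A quarter of the patients halves it to 1.40, and Φ(1.40 − 1.96) = 0.288.
- Directly: 3,140/4 = 785 patients, 7.5 per day, design effect 1 + 6.5 × 0.01 = 1.065. The effective number per arm is 785/2/1.065 = 368.5, SE = √(2/368.5) = 0.0737, and power is Φ(0.1125/0.0737 − 1.96) = 0.333.

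The second figure is higher because fewer patients per day share the day effect.

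**Patterns across four specialties with no true difference** (p = power of each test, tests treated as independent)
- Some but not all significant: 1 − p⁴ − (1 − p)⁴ = 0.736 for p = 0.288, and 0.789 for p = 0.333.
- ENT alone significant: p(1 − p)³ = 0.104 and 0.099.

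Specialties treated on the same day share that day's effect, so the tests are not fully independent. The implied correlation between two subgroup estimates is only 7.5 × 0.01/1.065 = 0.07.

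**Power of the direct comparison.** For an ENT share s, the SE of the ENT-versus-rest difference in treatment effect is 2√(1/(3,140s) + 1/(3,140(1 − s))), ignoring any day-to-day variation in that difference.

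| Assumed ENT share | SE | Power, difference 0.1125 SD | Power, difference 0.3 SD |
|---|---|---|---|
| 15% | 0.100 | 20% | 85% |
| 25% | 0.082 | 28% | 95% |
| 35% | 0.075 | 32% | 98% |

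**The case against.** The subgroups are declared exploratory. The primary analysis, the intention-to-treat set and the sample size do not depend on them. The word separately occurs only in the Discussion, which sets no significance rule, and separate estimates with confidence intervals can be combined into a difference. The analysis plan, which exists but is not shown, may contain an interaction test. All of this lowers the weight of the point. It does not remove it: no section reconciles the two lists, and the article names a method for the ENT question and attaches a mechanistic conclusion to it.

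Three stronger readings are tempting, and the documents do not support them.
- A reader might infer that trauma patients go unanalysed. They remain in the main models and in the age, sex, ASA and anaesthesia-type subgroup analyses. They lack only a surgery-type subgroup.
- A reader might infer that an ENT-only pattern would be mostly chance. The 74–79% refers to any mixed pattern. ENT alone is significant in about 10% of trials under the same assumptions, and how such a result should be read also depends on how plausible a true ENT-only effect is. The figures also borrow a length-of-stay effect for a question about pain.
- A reader might infer that the repair needs only new wording. The Protocol section says procedures are recorded in predefined bins with no re-identification, and the bins are not shown. If they do not separate the specialties, recoding may be impossible.

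**Conclusion.** The point holds as a moderate one about an exploratory analysis. The list mismatch is literal and rests on no assumption: as written, one prespecified subgroup has no eligible patients and one eligible specialty has no surgery-type subgroup. The ENT question is matched to a method that does not test it, and this follows from the Discussion's own wording. The percentages show only how easily separate tests can mislead. They assume equal specialty shares, equal effects and near-independent tests, and they are not predictions for pain. A direct test is the right tool but has limits: it is informative for differences near 0.3 SD and weak for differences near 0.11 SD.

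**What to change.** 1. Before analysis, reconcile the specialties in Patients with those in Statistical analyses. State explicitly whether plastic surgery cases are recruited and where trauma cases are placed. Use the same categories for the surgery-type covariate, as far as the recorded procedure bins allow.
2. For surgery type, add a treatment-by-surgery-type interaction to the planned mixed model with a random intercept for day. Report the ENT-versus-rest difference in treatment effect with its 95% confidence interval, alongside the specialty-specific estimates.
3. Reword the Discussion so that any ENT-only statement rests on that contrast and stays exploratory, and so that a non-significant interaction is not taken as evidence of a central mechanism.

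Cost: a short clarification and one added model term, with no change to the sample size. The open item is the recorded bins. The Trial status section expected recruitment to end in February 2026, so what the bins can distinguish should be checked first and any category that cannot be recovered should be reported. If the eligibility text is the list that has to change, that is a protocol correction and not only analysis-plan wording.
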